### Clinical assessments (see table 1)

**Table 1 T1:** Assessment schedule

	**GP or GP assistant**	**Patient**
**day 1 (baseline)**	Check availability	
	Obtain informed consent	
		Collect urine at GP surgery
	Perform dipstick and dipslide (and optionally sediment)	Fill in questionnaire
	Send urine to laboratory (refrigerated) for culture and sediment	

**day 2**	Examine dipslide	

**day 1 till day 7**		Record symptoms in diary

**day 8**	If patient did not use antibiotic: collect urine and send for culture	

After eligibility has been confirmed and informed consent has been obtained, urine is collected in a sterile container. Instructions for the collection method may be given at the GP's discretion, but are not necessary, as they have been reported to have no consequences for the extent of contamination. [50-52] We insist that the urine sample is collected at the GP surgery, since collection at home will cause at least some specimens to remain non-refrigerated for too long, thus rendering urinalysis unreliable.[53]

After urine collection, patients are asked to fill in a detailed questionnaire to record presence and severity of signs and symptoms (see additional file 1). Furthermore, they are given a special diary, in which they are to record clinical symptoms and any use of antibiotics for 7 days.

The GP or GP assistant performs a dipstick test (Multistix^® ^5, Siemens Medical Solutions Diagnostics™) and a dipslide test (Uricult^® ^classic, Orion diagnostica™). Dipsticks will be assessed automatically by a Clinitek Status^® ^analyzer (Siemens Medical Solutions Diagnostics™) to reduce inter-observer variation.

Immediately after dipstick and dipslide investigations have been performed, urine samples are stored in a refrigerator at the GP surgery. Within 8 hours they are transported to two laboratories (see below) at 4°C by a specialized courier service.

GPs are free to perform a urinary sediment investigation, the results of which will then be documented. However, in the statistical analysis we will assess the diagnostic value of the urinary sediment investigation performed by experts at the Laboratory for Clinical Chemistry of the Academic Medical Center in Amsterdam. Only if the sediment investigation proves to be useful under the optimal conditions of the laboratory, we will repeat it under daily practice conditions in a sub-study to be carried out after the main study has been completed (see further).

The Laboratory for Medical Microbiology of the Academic Medical Center in Amsterdam performs a urine culture, which serves as the reference standard. Trained laboratory technicians, who have no information on previous test results from history taking and/or urinalysis, will make a culture according to the standard loop method.[53], interpret the culture results and determine resistance patterns.

Patients who have not used antibiotics since their study entry will be asked to provide another urine sample for culturing at day 7 (see below).

Urine samples with a culture result ≥ 10^2 ^CFU/ml will be stored refrigerated for possible later use (e.g. identification of bacterial strains).

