## Substudies

### Prognosis

Using our diagnostic rule, the probability of a positive culture at baseline can be estimated. For a clinician it may also be relevant to learn more about a patient's prognosis and how this is affected by antibiotic medication. In previous studies 25 to 50% of women presenting with UTI symptoms and/or bacteriuria have been reported to recover spontaneously within one week. [43-45] It would be useful to know whether these patients, for whom antibiotics are not indicated, can be identified at baseline based on their clinical profiles.

In ACUTIS, all patients are asked to record their symptoms and possible antibiotic use in a special diary for 7 days. To learn more about the natural course of UTI, we will offer eligible women the opportunity to postpone the use of antibiotics. For patients who have not used antibiotics after 7 days, we shall try to secure a second urine specimen for culture. As a result, two prognostic models may be developed, with clinical and bacteriological cure after one week serving as dependent variables, respectively. Regression analysis will be used to assess the effects of antibiotic treatment using all cogent potential confounders to counteract possible confounding by indication as much as possible. If in specific subdomains of women no effect of antibiotics is found, randomised trials may be indicated to confirm such findings. If, on the other hand, an effect is found, the effect may be non-existent in particular subgroups. However, the power to detect such subgroup effects (or a lack of it) is probably somewhat limited. Women with milder symptoms may be more likely to defer antibiotics. We consider this not to be a great problem, since this is the subdomain of patients in which doubt about the value of antibiotics is greatest. Placebo-controlled randomized clinical trials in the subdomain of patients with severe dysuria and/or frequency are likely to incur ethical problems. If our results are promising, however, an RCT may be performed in the future (possibly by using a delayed prescription approach. [67-69]).

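### The second culture is limited to women who stay off antibiotics all week, so the bacteriological-cure model is likely, though not certain, to overstate untreated cure for a woman assessed at day 1

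*Protocol article*

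**What the plan says.** The restriction appears three times in the protocol article.

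- Clinical assessments, text: "Patients who have not used antibiotics since their study entry will be asked to provide another urine sample for culturing at day 7".
- Clinical assessments, Table 1: "If patient did not use antibiotic: collect urine and send for culture".
- Substudies, Prognosis: "For patients who have not used antibiotics after 7 days, we shall try to secure a second urine specimen for culture".

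Antibiotic use is not randomised. In the Prognosis section, "we will offer eligible women the opportunity to postpone the use of antibiotics". Nothing holds a woman to a full week without treatment, and the diary records symptoms and any antibiotic use over the 7 days.

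The same section gives the purpose of the second sample: "two prognostic models may be developed, with clinical and bacteriological cure after one week serving as dependent variables, respectively". It also plans an adjustment: "Regression analysis will be used to assess the effects of antibiotic treatment using all cogent potential confounders". It concedes one form of selection, "Women with milder symptoms may be more likely to defer antibiotics", and adds: "We consider this not to be a great problem".

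The prognostic index is for use at presentation. The Background section on prognosis has the GP estimating the 7-day course and deciding who is likely to benefit from treatment. The Prognosis section asks whether spontaneous recoverers can be recognised at baseline.

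A side point: the text places the second sample at day 7 and Table 1 lists it under day 8. These should be reconciled, but nothing below turns on it.

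**The concern.** An offer to postpone leaves room for a later start. A woman who postpones, stays unwell and begins an antibiotic on, say, day 3 gives no second culture. A woman with the same baseline profile who improves and never starts does give one. Membership of the bacteriological-cure data set is thus settled during follow-up, by behaviour that may be related to the outcome.

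The GP using the index has only baseline information and cannot know who will stay untreated. A model fitted to women who stayed untreated answers a different question: how often bacteriuria clears among those who turned out not to need, or not to want, an antibiotic. If that proportion is read as the chance of clearing without treatment for any woman who postpones, some women would appear more likely to clear untreated than the data support.

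**Working it through.** **Do the plan's own provisions deal with this?**

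- The remark on milder symptoms concerns who chooses to defer. It does not cover women who defer, fail to improve and then start.
- The regression adjustment is aimed at confounding by indication. Baseline covariates can absorb starting that is driven by baseline severity, but not starting driven by the course of the week. Under the stated rule no woman who took an antibiotic has a second culture, so an antibiotic effect on bacteriological cure cannot be estimated from these data.
- The Missing values section gives generic multiple imputation by chained equations and says nothing specific about the second culture. For a woman who started antibiotics, an untreated end-of-week culture does not exist.

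**How large could the effect be?** The article gives no figure for second-culture numbers, start rates or culture clearance, so there is no stated figure to reproduce. All inputs are assumptions:

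- t, true untreated clearance at one week: 25%, 37.5%, 50%. The article's 25 to 50% describes recovery, not culture clearance, and is borrowed only as a plausible range.
- q1, chance that a woman who would clear starts an antibiotic in the week: 10%.
- q0, the same chance for a woman who would not clear: 30% or 50%.

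Share with a second culture = t(1 − q1) + (1 − t)(1 − q0).

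Observed cure = t(1 − q1) / [t(1 − q1) + (1 − t)(1 − q0)].

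Example with t = 0.25, q1 = 0.10, q0 = 0.50: 0.225 / (0.225 + 0.375) = 0.225 / 0.600 = 37.5%.

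| True t | q1 | q0 | Share cultured | Observed cure | Difference (points) |
|---|---|---|---|---|---|
| 25% | 10% | 30% | 75% | 30.0% | +5.0 |
| 37.5% | 10% | 30% | 78% | 43.5% | +6.0 |
| 50% | 10% | 30% | 80% | 56.2% | +6.2 |
| 25% | 10% | 50% | 60% | 37.5% | +12.5 |
| 37.5% | 10% | 50% | 65% | 51.9% | +14.4 |
| 50% | 10% | 50% | 70% | 64.3% | +14.3 |
| any of these | 20% | 20% | 80% | equal to t | 0 |
| 25% to 50% | 30% | 10% | 80% to 85% | 20.6% to 43.7% | −4.4 to −6.3 |

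The last row shows that the sign depends on who starts more often.

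**A version in which only symptoms drive starting.** Let symptoms improve in a proportion a1 of clearers and a0 of non-clearers, and let antibiotics be started by s1 of improved and s0 of unimproved women. The chance of staying untreated is k1 = a1(1 − s1) + (1 − a1)(1 − s0) for clearers; k0 is the same with a0. Observed cure = t·k1 / [t·k1 + (1 − t)·k0].

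- a1 = 0.7, a0 = 0.4, s1 = 0.1, s0 = 0.5, t = 0.25: k1 = 0.78, k0 = 0.66, observed 28.3% (+3 points).
- a1 = 0.8, a0 = 0.3, s1 = 0.05, s0 = 0.7, t = 0.50: k1 = 0.82, k0 = 0.495, observed 62.4% (+12 points).
- a1 = a0: k1 = k0, and the difference is 0.

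**The case against.** Several points on the other side stand.

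- **Direction.** A reader might infer that the cultured group is selected on improvement and that the model is bound to overstate cure. The documents do not support that. The filter is antibiotic use, which also reflects baseline mildness and preference. Upward bias needs women with persisting bacteriuria to start more often, and no passage shows this.
- **Size.** A reader might take 25 to 50% as the document's own clearance rate. It is a recovery rate, and the start rates are assumed as well. The formula is also marginal, whereas the planned model conditions on the baseline profile. Selection explained by baseline predictors can be partly handled there; what remains is selection arising during the week.
- **Reach.** A reader might extend the bias to all natural-course results and both prognostic models. The clinical-cure model rests on diaries that all patients are asked to keep, so this filter does not touch it. The primary diagnostic objective uses the baseline culture and is unaffected.
- **Weight.** This is a substudy with models that may be developed, and the article says randomised trials may be needed to confirm any subgroup without an antibiotic effect. Nothing says that cure among never-starters will be reported, unqualified, as the natural course.
- **Detail left elsewhere.** Handling of starters could sit in a fuller plan. That is fair for the analysis method, but not for the sampling rule, which the article fixes in three places.

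None of this answers the core point: outcome availability is set after baseline, and the article's remarks on selection do not address starting within the week.

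**Conclusion.** The point holds in a limited form. Inclusion in the bacteriological-cure model depends on remaining off antibiotics for the whole week, while the index is to be read at day 1. On the expected but undocumented assumption that non-clearers start antibiotics more often than clearers, the model is likely to overstate untreated bacteriological cure. With assumed start rates of 10% against 30-50% and assumed clearance of 25-50%, the overstatement is about 5 to 14 percentage points. It is zero with equal start rates and would reverse if clearers started more often. The actual size cannot be obtained from the document. The finding is confined to this one substudy model and should be corrected before that model is fitted.

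**What to change.** 1. Define the analysis set at day 1 as women with a positive baseline culture who postponed antibiotics.
2. Report how many of them started antibiotics during the week, with their diary symptoms beforehand, and how many untreated women gave no second sample. The article promises only to try to obtain it.
3. Fit the bacteriological-cure model with inverse-probability weights for remaining untreated and sampled, estimated from baseline tests and daily diary symptoms. State the assumption that these variables capture the reasons for starting and for not being sampled.
4. In the same set, report the proportion with no antibiotic used and a negative second culture as a conservative lower bound. Missing second cultures among untreated women are imputed or counted as not cured; counting them as not cured is the stricter choice. With 10% of clearers starting, a true 35% would show as 0.35 × 0.90 = 31.5%.
5. State that unweighted cure among never-starters applies only to women who stay untreated and is not the natural course.

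The restriction to baseline-positive women in steps 1 and 4 is essential. Women enter on symptoms, and the Sample size section assumes that only about half have a UTI at the 10^5 CFU/ml cut-off. As an illustration, suppose half the set were baseline-negative, all of these stayed negative and 10% of them started antibiotics. The unrestricted proportion would be 0.5 × 0.90 + 0.5 × 0.315 = 61% against a true 35%, and would no longer be a lower bound.

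Cost: a little more analysis work on data already planned, less precise weighted estimates and a smaller denominator.

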### Data entry

The information obtained from patient history and laboratory investigations will be collected and entered into a structured database by a qualified commercial data-entry service, which guarantees a 97% accuracy at character level. For crucial variables (e.g. culture results) there will be double (independent) entry (99.7% accuracy at character level).

## Statistical analysis

### Data screening

The data will be screened for data entry errors, extreme values, and missing values using simple tables, plots, and dedicated commands to identify (multivariable) outliers. Errors will be corrected. Instead of deleting extreme cases, we shall consider to suitably truncate extreme values where their influence on models appears too strong.[54]

### Missing values

Multiple imputation using chained equations will be used to impute missing values.[55,56]

### Dependent variable

The results of the urine culture will be used as the dependent variable. A cut-off value of 10^3 ^CFU/ml will be used to define a positive culture, as is recommended by the European Urinalysis Guidelines.[42] We will explore how sensitive the model is to the use of different cut-off values for defining a positive culture.[6,12,57-60]

Theoretically, false positive reference standard results may occur if women with asymptomatic bacteriuria are included in the study when they visit their GP with complaints similar to UTI symptoms but caused by a different disease (e.g. vaginitis). In the community, the prevalence of asymptomatic bacteriuria has been reported to be 1 to 5% in premenopausal, nonpregnant women, growing with increasing age to >10% in women over 70 years of age.[61]

### Variable selection strategy

#### General objectives

We aim to generate two models (diagnostic indices). First, a model which assumes that patients attend the GP surgery. Second, a model based on telephone contact only, since in daily routine this is very often the first and only contact with the patient.

Finally, using different threshold probabilities for 'no further action' (e.g. advice to increase the intake of water, 'wait and see') and prescription of an antibiotic, respectively, we will develop a diagnostic test algorithm such that patients may undergo the least number of possible tests. That is, if, regardless of its results, a certain test can be shown not to take a patient across one of the abovementioned thresholds for specific clinical action, that test may be informative, but not sufficiently so to change management. Therefore it is superfluous. It is possible that a 'telephone only' model provides sufficient certainty for patients with specific combinations of patient history items, while for other patients urinalysis at the GP surgery is needed to decide on management correctly.

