### Diagnostic work-up

Diagnosis of UTIs in general practice consists of various medical history questions and laboratory investigations, of which nitrite and leukocyte esterase (LE) dipstick tests, microscopic examination of urinary sediment, and dipslide are the ones most widely used.

Most diagnostic tests for UTIs have been studied before in single-test evaluations, implying that a test is compared to the urine culture, not taking into account the distribution of other test results in the population studied. [17-19] In practice, however, the diagnostic work-up is inherently multivariable, and test results are mutually dependent. [20-36] Therefore it cannot be generally expected that a test's sensitivity is invariant over different degrees of prior testing. For example, the sensitivity of the nitrite dipstick test will be affected by the information contained in the diagnostic profile resulting from prior test results.[37]

The primary objective of the Amsterdam Cystitis/Urinary Tract Infection Study (ACUTIS) is to determine the (additional) diagnostic value of relevant tests from patient history and laboratory investigations, taking into account their mutual dependencies. Next, an easy to use, multivariable diagnostic rule (clinical index) will be derived. After suitable (external) validation, GPs may use the (validated) rule to estimate UTI probabilities for women with different combinations of test results.

Little et al. and McIsaac et al. described similar work in a UK and a Canadian population, respectively.[38,39] However, different inclusion criteria were used (see further) and urine samples were transported as in routine practice before cultures were made, whereas in ACUTIS, to assure reliability of the cultures (= reference standard), urine samples are being refrigerated until being cultured. Furthermore, both earlier studies did not assess diagnostic values of the sediment and dipslide investigations.

Other similar studies.[40,41] were performed before the European Urinalysis Guidelines.[42] recommended a cut-off value of 10^3 ^cfu/ml for significant *Escherichia coli *bacteriuria and therefore only used the traditional cut-off value of 10^5 ^cfu/ml. Besides, they did not assess dipstick investigations and/or were not performed in a primary care setting.[41]

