### Design

In a prospective cohort, each participating patient will be followed for 7 days. At baseline, potentially relevant signs and symptoms will be recorded and potentially relevant laboratory tests (dipstick, sediment and dipslide) will be performed, along with a urine culture as reference test. Details are described below.

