### Sample size

When the events per variable (EPV) rule.[46,47] is applied on a number of 15 possible diagnostic indicators and taken into account that some indicators will have to be modeled as dummy variables, about 200 women with a UTI are needed for this study (although a more recent simulation study suggests that the traditional EPV figure may be an overestimate.[48], so that less patients may be needed for our study). Assuming that the probability of a UTI (if defined by ≥ 10^5 ^CFU/ml) in eligible women is approximately 50%.[11,12] (range 40–60%), between 333 and 500 women will have to be included in the study. According to a UTI incidence in The Netherlands of 68 per 1000 women per year.[49], 157 women per year are diagnosed with a UTI in a general practice of average size. Assuming that 80% of all eligible women will not take part in the study, 16–17 practices of average size that include patients for a period of 1 year are needed (500/(157 × (1-0.8)) = 16.03).

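### Read literally, the test-saving rule judges each test alone, so it can discard tests that would change management in combination

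*Protocol article*

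**What the plan says.** After the two diagnostic models, the protocol article (Variable selection strategy, General objectives) announces a further product: "we will develop a diagnostic test algorithm such that patients may undergo the least number of possible tests". It is to be built "using different threshold probabilities for 'no further action" and for prescribing an antibiotic. No threshold values are given.

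The article then defines which tests may be left out. The condition is that "regardless of its results, a certain test can be shown not to take a patient across one of the abovementioned thresholds". The consequence is that "that test may be informative, but not sufficiently so to change management. Therefore it is superfluous".

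The section closes by contrasting women whose history alone may give enough certainty by telephone with others who need urinalysis at the surgery.

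The Design section lists what is available beyond history: "potentially relevant laboratory tests (dipstick, sediment and dipslide) will be performed". The Background (Diagnostic work-up) sets the aim of determining the additional value of tests, "taking into account their mutual dependencies".

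**The concern.** The definition refers to one test and to that test's own results. It grants that such a test may carry information and still discards it. Nothing in the section provides for looking ahead to a second test, for judging the remaining tests as a set, or for returning to a discarded test once other results are known.

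Failing to cross a threshold alone does not imply failing to cross it jointly, because evidence from several tests accumulates on the log-odds scale. If every remaining test fails singly, the literal rule drops all of them, even where the set would have settled management.

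The study's rationale is that tests should not be evaluated one at a time. The models respect this, but the elimination step as worded does not. The algorithm is the output that would tell GPs what to omit, and the Discussion already anticipates that urine tests may add nothing for many women. A criterion that leans towards omission should therefore be stated correctly.

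**Working it through.** The article gives no figure for this step, so there is none to reproduce. The check uses Bayes' theorem: post-test odds = pre-test odds × product of likelihood ratios (LRs).

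**Inputs.** The pre-test probability is taken from Sample size, where the UTI probability "in eligible women is approximately 50" per cent (range 40–60%). That figure refers to the 10^5 CFU/ml definition, whereas the outcome uses 10^3, so it serves only as a starting value. Thresholds, accuracies and conditional independence given culture status are assumptions for illustration.

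**Main example.** Thresholds 30% and 70%; two tests with LR+ 2 and LR− 0.5, which corresponds to sensitivity = specificity = 2/3.

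- Pre-test odds: 0.5/0.5 = 1.
- One test: odds 2 gives 2/3 = 67%; odds 0.5 gives 1/3 = 33%. Neither crosses, so each test is superfluous under the literal rule.
- Both positive: odds 4 gives 80%. Both negative: odds 0.25 gives 20%. Both cross.
- Share of women in whom the two agree: (2/3)² + (1/3)² = 5/9 = 56%.

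The rule as written classifies 0% of these women; both tests together classify 56%.

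**Dependence on the pre-test probability.** One test fails to cross only while odds × 2 < 7/3 and odds × 0.5 > 3/7, that is, for odds between 0.857 and 1.167 (46% to 54%). At 40% a negative result gives odds 0.667 × 0.5 = 0.333, or 25%. At 60% a positive result gives odds 1.5 × 2 = 3, or 75%. Each crosses alone, so in this example the tests are not dropped at either end of the protocol's range.

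**Other assumed inputs** (share of women classified):

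| Thresholds | Tests (sens = spec) | Pre-test | Rule as written | All tests |
|---|---|---|---|---|
| 20/80 | two at 0.75 | 50% | 0% | 0.75² + 0.25² = 62.5% |
| 20/80 | two at 0.70 | 50% | 0% | 0.70² + 0.30² = 58% |
| 20/80 | two at 0.70 | 40% or 60% | 0% | 33% |
| 20/80 | three at 0.70 | 40, 50 or 60% | 0% | 0.70³ + 0.30³ = 37% |
| 10/90 | three at 0.75 | 40, 50 or 60% | 0% | 0.75³ + 0.25³ = 44% |
| 10/90 | two at 0.70 | 40, 50 or 60% | 0% | 0% (no loss) |

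The 33% at a pre-test probability of 40% arises because only the double negative crosses: 0.4 × 0.30² + 0.6 × 0.70² = 0.036 + 0.294 = 0.33. With thresholds 30/70 and tests at 0.70 or 0.75, each test crosses alone at 40, 50 and 60% (exactly at the boundary for 0.70 at 50%), so nothing is dropped at the outset.

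**Dependence between tests.** Let r be the correlation of the two results within each culture group.

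- Main example: the probability after two positives is (4 + 2r)/(5 + 4r). It equals 0.70 when 4 + 2r = 3.5 + 2.8r, so r = 0.625. Agreement becomes more frequent as r rises, 5/9 + 4r/9, but above about 0.63 it no longer crosses and nothing is lost by dropping the pair.
- Thresholds 20/80, two tests at 0.70, pre-test 50%: (0.49 + 0.21r)/(0.58 + 0.42r) = 0.80 gives 0.026 = 0.126r, so r = 0.206. Above about 0.21 the 58% falls to 0.

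**The case against.** The strongest reply is that this sentence is a gloss on an aim, in a condensed article, about an algorithm still to be developed. It fixes no order of testing and no stopping rule. It can also be read conditionally: a test is superfluous if it cannot move the woman across a threshold given her other results. Under that reading the loss does not arise, and it fits the stated interest in additional value. This stands as a possible intention. It does not remove the point, because the article states a criterion, and its words describe a single test and that test's own results.

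A reader might infer that women will be left undecided and untested, or that the share manageable by telephone will be overstated. The documents do not support this. The section's closing sentence sends women without sufficient certainty to urinalysis as a block. That sentence describes a possible outcome and does not amend the definition, but it shows that the authors do not intend to leave such women without tests.

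A reader might also infer that the algorithm would drop one pad of the strip, since the Background names "nitrite and leukocyte esterase (LE) dipstick tests" separately. That passage describes general practice. Design and Clinical assessments treat the dipstick as one test, and nothing says that a single pad would be omitted.

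Finally, the illustrations assume conditional independence, which the study itself doubts. That is fair: moderate dependence can remove the gain.

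**Conclusion.** The point holds as a fault in a stated rule. Followed literally, the criterion can discard informative tests that would together change management, and this logic needs no numerical assumption.

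How often it would happen in this cohort cannot be derived from the document. It depends on the thresholds, the test accuracies, the spread of probabilities after history taking and the dependence between tests. In the illustrations the share of women affected runs from nil to 62.5%, and these figures are not estimates for the trial.

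The consequence is limited to the test-saving algorithm. Data collection, sample size and the two diagnostic models are untouched. The wording should be corrected before the algorithm is built.

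**What to change.** Replace the one-test criterion with a joint one:

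- For a given profile, assess sets or sequences of the tests still available (dipstick, sediment, dipslide), using joint result probabilities from the fitted multivariable model.
- Call a test or set superfluous only if omitting it leaves management the same as under the full work-up, apart from a prespecified small share of women. The tolerance matters: keeping a test for the sake of one very rare combination of results would defeat the aim of sparing tests.
- Report the share of women left between the thresholds under the reduced algorithm and under the full work-up.

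If the conditional reading was intended, this wording makes it explicit. The cost is a paragraph of text and an enumeration of result combinations. No new data are needed, since the design already provides for all three laboratory tests. The downside is that some fewer tests may be declared superfluous.
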